## Abstract

**Background:**

Diabetes self-management education and support (DSMES) is a crucial component of diabetes care associated with improved clinical, psychosocial, and behavioral outcomes. The American Association of Diabetes Care and Education Specialists, the American Diabetes Association, and the American Academy of Family Physicians all recommend DSMES yet accessing linguistically and culturally appropriate DSMES is challenging in rural areas. The Diabetes One-Day (D1D) program is an established DSMES group intervention that has not been adapted or evaluated in rural communities.

**Objective:**

The specific aims of this paper are (1) to adapt the existing D1D program for use in rural communities, called rural D1D (R-D1D); and (2) to conduct a patient-level randomized controlled trial to examine the effects of R-D1D and standard patient education, guided by the Reach, Effectiveness, Adoption, Implementation, and Maintenance framework.

**Methods:**

This is a protocol for a pilot type II hybrid implementation-effectiveness trial of a culturally adapted virtual DSMES program for rural populations, R-D1D. We will use Boot Camp Translation, a process grounded in the principles of community-based participatory research, to adapt an existing DSMES program for rural populations, in both English and Spanish. Participants at 2 rural primary care clinics (4 cohorts of N=16 plus care partners, 2 in English and 2 in Spanish) will be randomized to the intervention or standard education control. The evaluation is guided by the Reach, Effectiveness, Adoption, Implementation, and Maintenance framework. Patient-level effectiveness outcomes (hemoglobin A_1c_, diabetes distress, and diabetes self-care behaviors) will be assessed using patient-reported outcomes measures and a home A_1c_ test kit. Practice-level and patient-level acceptability and feasibility will be assessed using surveys and interviews.

**Results:**

This study is supported by the National Institute of Nursing. The study procedures were approved, and the adaptation processes have been completed. Recruitment and enrollment started in July 2021.

**Conclusions:**

To our knowledge, this will be the first study to evaluate both effectiveness and implementation outcomes for virtually delivered DSMES, culturally adapted for rural populations. This research has implications for delivery to other rural locations where access to specialty diabetes care is limited.

**Trial Registration:**

ClinicalTrials.gov NCT04600622; https://clinicaltrials.gov/ct2/show/NCT04600622

**International Registered Report Identifier (IRRID):**

DERR1-10.2196/34255

## Introduction

### Diabetes and Rural Populations

Diabetes mellitus is a chronic, progressive disease affecting 30.3 million people in the United States [1]. In addition to being the 7th leading cause of death in the United States, diabetes contributes to serious microvascular and macrovascular complications [1]. Diabetes self-management is the cornerstone to avoiding or delaying diabetes complications, and ongoing self-management is necessary. Self-management behaviors involve an often-challenging daily diet, medication, exercise, and glucose monitoring regimen, among others, and is complicated by social determinants of health (eg, transportation and access to high-quality care). Diabetes self-management education and support (DSMES) is a crucial component of diabetes care that provides the foundation necessary to self-manage diabetes. The American Association of Diabetes Care and Education Specialists, the American Diabetes Association, and the American Academy of Family Physicians all recommend DSMES [2]. DSMES can improve outcomes in both type 1 (T1D) and type 2 diabetes (T2D), including improving hemoglobin A_1c_, quality of life, diabetes distress, and healthy coping [3-6]. However, there is variation in how DSMES interventions are structured, in terms of both content and delivery, and as such, some DSMES programs may be more acceptable, feasible, and effective than others [7].

Approximately 50% of adults with T1D [8] and 90% of adults with T2D in the United States are managed in primary care settings and not in endocrinology specialty practice offices [9], and therefore often lack access to services such as DSMES. Strikingly, 75% of counties in the United States have no endocrinologists at all, while primary care can be found in 96% of US counties [10]. Especially in rural areas, many people with diabetes receive their diabetes care at primary care practices and may have to travel long distances to access DSMES when not available in their medical home. When DSMES is available, there can be a lack of fit between the curriculum, materials, or mode of delivery and the resources of rural primary care practices and communities, including a lack of staff and lack of information tailored to the resources and culture in rural communities. There is a clear need for DSMES interventions, feasible for delivery in rural settings, that can address the unique social determinants of health and cultural adaptations appropriate for people with diabetes living in rural communities.

The 2017 National Standards for DSMES recommend a multidisciplinary team delivering DSMES, a curriculum reflecting current evidence and practice guidelines, individualized plans, and sources for ongoing support [11]. Personalizing care via DSMES is critical because it allows individuals to identify how to incorporate self-management into their own daily life [12,13]. While individual DSMES may be better suited for personalized approaches to care, group sessions can be more cost-effective than individual sessions [14] and offer opportunities for peer support. However, when sessions are held over several weeks, it can be challenging for individuals to complete leading to attrition [15]. A systematic review of 118 unique DSMES interventions found that patients who receive group and individual DSMES sessions, from multidisciplinary teams, are the most effective at reducing A_1c_ [15]. Interventions that address the need for group and personalized care can reduce disparities in rural populations. This study will address current gaps in rural diabetes care research and a widely recognized need to enhance access to DSMES among rural populations.

National data indicate that diabetes prevalence is higher in rural areas. Rural-dwelling adults are 17% more likely to have diabetes than their urban counterparts nationally [16]. For instance, the rates of diabetes in rural eastern Colorado average 12.3% compared to the state average of 7.3% [17]. Rural populations have limited access to DSMES, and health care access is more limited in rural areas, impeded with long travel distances, as well as higher rates of poverty than those individuals in urban settings [14]. These challenges contribute to a greater risk of suboptimal diabetes management and higher rates of diabetes-related complications [18]. The Diabetes One-Day (D1D) intervention is a condensed, one-day group DSMES session delivered via telehealth by a multidisciplinary team at a diabetes and endocrinology center. Patients are encouraged to invite a care partner (family member or friend) to attend D1D given that diabetes is managed in a social context. D1D was designed to address DSMES access challenges seen with multiple-day DSMES interventions. Evidence suggests that the D1D intervention is effective for improving diabetes self-management outcomes [19,20] and is a promising intervention to address specialty care access challenges seen in rural communities. Further consideration of cultural and social adaptations to D1D (ie, a Rural D1D [R-D1D] program) is needed to ensure fit for rural communities, especially those where English and Spanish are the primary languages spoken. We describe our protocol for adapting D1D for rural primary care and implementing, evaluating, and refining the resulting R-D1D intervention.

### Intervention Logic Model

The logic model for this project (Figure 1) depicts the process by which the D1D intervention (Box A) is adapted, implemented, and refined for rural settings (R-D1D, Box B), to promote the successful adoption and implementation by rural practices and reach to patients in the target audience (Box C). Once adopted and implemented, a future study will assess effectiveness for patient-reported and clinical outcomes at the patient level and maintenance at the practice level (Box D). That is, to achieve impact on patient-level outcomes and to be sustainable for practices, the intervention must be acceptable, appropriate, and feasible for delivery in rural primary care, be implemented well, and reach target populations. The intermediate outcomes and impact outcomes align with the Reach, Effectiveness, Adoption, Implementation, and Maintenance (RE-AIM) framework, a well-established framework for program planning and evaluation [21].

**Figure 1 figure1:**
[figure not shown]
Intervention logic model. D1D: Diabetes One-Day; R-D1D: Rural Diabetes One-Day.

### Aims and Hypothesis

The coprimary aim of this study is to adapt the existing D1D program for use in rural communities (R-D1D). Boot Camp Translation (BCT) [22,23] will be used to partner with diverse community members, including members from Spanish-speaking communities, to adapt diabetes self-management language and tools and delivery of D1D into a culturally relevant R-D1D for rural primary care practices, patients, and care partners.

The secondary coprimary aim is to conduct a patient-level pilot randomized controlled trial (RCT) to examine the effects of R-D1D (intervention group) vs standard patient education (attention control group), guided by the RE-AIM framework. We will implement and refine the R-D1D intervention, evaluate implementation at the practice level, and evaluate reach and effectiveness at the patient level.

## Methods

### Design

This study will use the BCT method to adapt the medical information, guidelines, and materials in the current D1D intervention for use with English-speaking and Spanish-speaking people living in rural eastern Colorado (R-D1D). Then, using a 1:1 type 2 hybrid trial, we will conduct a pilot test in 64 total patients from 2 practices to compare R-D1D to a standard education control. Acceptability and feasibility of R-D1D will be assessed at the patient and practice levels.

### Setting

This project will take place in the High Plains Research Network, a practice-based research network of 53 primary care practices, hospitals, and communities in a 16-county region of rural eastern Colorado. Two High Plains Research Network primary care clinics will be included. To participate, clinical practices must be willing to identify and refer potential English-speaking and Spanish-speaking participants with T1D or T2D to the research team at the University of Colorado for eligibility screening and informed consent.

### Sample and Recruitment

#### Provider and Staff

Practice providers and staff participants will be individuals (N=3 per clinic) who work at 1 of the 2 rural clinics where R-D1D will take place. A sample of providers and staff will be asked in person, by phone, or by email to participate in key informant interviews.

#### Patient and Care Partner

English-speaking and Spanish-speaking adults with T1D and T2D living in the proposed study region (N=64) and care partners in the intervention group (up to N=16) will be eligible for participation. We will use both community recruitment in venues identified during the BCT, as well as work with each of the 2 participating practices to help identify patients with diabetes who will then be randomized to either the intervention or attention control arm. They will be recruited using strategies recommended by the BCT participants, building upon successful recruitment strategies used in past projects. For instance, practices will distribute recruitment materials with messages created by the community-academic partnership through BCT and design elements selected by the community. This sample size is appropriate for iterating the intervention.

### Eligibility Criteria

#### Provider and Staff

Participants will be eligible if they work at the rural clinic where R-D1D will take place and if they were involved with the planning or coordination of R-D1D or were a provider who had a patient participate in the R-D1D intervention. Possible participants could include physician, nurse, medical assistant, front desk support, and clinic administrator. There are no exclusion criteria for providers and staff.

#### Patient Participant

Participants will be eligible for inclusion if they (1) have a known diagnosis of T1D or T2D with any A_1c_ level; (2) are ≥18 years old; (3) live in a rural eastern Colorado; (4) speak and understand English or Spanish; and (5) are willing to participate in a telehealth intervention at home through Health Insurance Portability and Accountability Act (HIPAA)-compliant Zoom. Participants will be excluded if they (1) are participating in another diabetes study; (2) have significant cognitive impairment; (3) are pregnant or planning to become pregnant in the next year (as diabetes management recommendations are different in pregnancy); (4) have life expectancy of <6 months; or (5) plan to move during the time of the study.

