### Adapted R-D1D Intervention

R-D1D will be delivered by an interdisciplinary team of health care professionals specifically trained in the D1D program, including a nurse practitioner, physician, registered dietitian, certified diabetes care and education specialist, pharmacist, and a licensed clinical social worker. The R-D1D program will be delivered by telehealth by members of the original D1D team. An overview of the D1D curriculum that will be adapted is detailed in Multimedia Appendix 1.

Intervention group participants will meet with study staff to assess the participant’s technology literacy, test the participant’s internet connection and chosen electronic device, and provide instruction and demonstration for connecting to the videoconference platform. More than 1 meeting may be required. These meetings will be held via the same platform used for R-D1D intervention to allow the opportunity to troubleshoot directly with the participant.

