### Outcomes and Measures

The outcomes for this study are informed by the Reach, Effectiveness, Adoption, Implementation and Maintenance (RE-AIM) framework [32]. We will use multiple methods (qualitative and quantitative) to assess select RE-AIM domains. Reach and Effectiveness are both patient-level outcomes. Reach refers to the number and percent of eligible patients who participate in the intervention, characteristics of those who participate and complete the measures, and reasons for not participating. Effectiveness refers to clinical and behavioral patient-level outcomes. Adoption, Implementation, and Maintenance are practice-level outcomes (maintenance can also refer to patient-level maintenance of health outcomes over time). Adoption refers to the number, percent, and characteristics of clinical practices who were invited to offer the intervention to their patients who participate in the study. Implementation refers to consistency of delivery of the intervention as intended (ie, fidelity), as well as practice perceptions of the acceptability, appropriateness, and feasibility of delivering the intervention in their clinical practice setting [33]. Maintenance refers to sustained effects on patient outcomes over time and to continued intervention delivery within the clinical setting beyond the study period, which will be explored in a future study.

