#### Patient-Level Reach

We will capture data on R-D1D attendance, percent of R-D1D sessions attended, R-D1D program satisfaction, and patient reasons for participating and not participating.

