### Statistical Methods and Analyses

#### Quantitative Analysis for RCT

Evaluating Reach will include description of the characteristics of those enrolled and screened ineligible and provide preliminary data on recruitment and retention capabilities for future studies. Quantitative metrics for recruitment and retention rates will inform population point estimates and 95% confidence intervals. For example, a 70% retention of 64 participants leads to a point estimate and CI of 70% (SD 6).

Descriptive statistics will be used to summarize R-D1D reach, adoption, and implementation at the participant and practice level. Special attention will be used to stratify outcome measures based on diabetes type, gender, and clinic site. For quantitative measures on feasibility, appropriateness, and acceptability, we will use the validated scales by Weiner et al [33]. Each of the 3 domains is composed of 4 Likert-scale questions (Completely Disagree 1 to Completely Agree 5). Our benchmarks for success will be to obtain domain means of 4 or greater.

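### Willingness to use telehealth is part of eligibility, and Reach is a percent of eligible patients, so patients who refuse because the program is virtual leave the Reach denominator

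*Protocol article*

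**What the plan says.** Five places in the protocol article bear on this.

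- **Eligibility Criteria, Patient Participant.** The fifth inclusion criterion requires that patients "are willing to participate in a telehealth intervention at home" over Zoom. Criteria 1 to 4 cover diagnosis, age, residence and language.
- **Outcomes and Measures.** "Reach refers to the number and percent of eligible patients who participate in the intervention". The same sentence adds participant characteristics and reasons for not taking part.
- **Patient-Level Reach.** The data to be captured include attendance, satisfaction and "patient reasons for participating and not participating".
- **Quantitative Analysis for RCT.** The evaluation of Reach will include "description of the characteristics of those enrolled and screened ineligible". The section also says: "Quantitative metrics for recruitment and retention rates will inform population point estimates and 95% confidence intervals".
- **Adapted R-D1D Intervention.** "The R-D1D program will be delivered by telehealth by members of the original D1D team". No other mode of delivery is offered.

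**The concern.** Criteria 1 to 4 describe whom the program is for. Criterion 5 describes whether a person accepts the way it is delivered. Acceptance of the delivery mode is a large part of what Reach should measure when the program is virtual, so a denominator restricted to people who have already accepted it is partly circular.

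Reach is one of the outcomes named under the second coprimary aim, and the logic model treats reaching the target population as a precondition for impact. A Reach percentage computed by the stated rule would look better than the share of suitable rural patients who actually take up the program. A reader could not recover that share from the percentage alone.

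**Working it through.** **The plan's own figure.** There is none to reproduce. The article gives no Reach percentage, no number screened and no share refusing telehealth. Its one worked percentage, 70% of 64, concerns retention and has no bearing here.

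**Step 1: classify one patient.** Take a patient who meets criteria 1 to 4, has no exclusion and declines because the session is by video.

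- By Patient Participant, criterion 5 fails, so the patient is not eligible.
- By Outcomes and Measures, Reach counts eligible patients, so the patient is not in the denominator.
- By Quantitative Analysis for RCT, the patient may be described among the screened ineligible, but that description does not enter the percentage.

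**Step 2: the size of the effect.** Let

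- E = patients meeting criteria 1 to 4 with no exclusion,
- u = the share of E who refuse telehealth at home,
- n = participants.

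Reach as the protocol defines it = n / [E(1-u)].

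Reach with refusals kept in = n / E.

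Ratio of the first to the second = 1/(1-u). Both n and E cancel.

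**Step 3: illustration.** E and u are assumptions. n = 64 is the planned trial size (Design: "we will conduct a pilot test in 64 total patients from 2 practices").

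| Assumed u | Factor 1/(1-u) | E = 200 (n/E = 32.0%) | E = 128 (n/E = 50.0%) |
|---|---|---|---|
| 0% | 1.00 | 32.0% | 50.0% |
| 10% | 1.11 | 64/180 = 35.6% | 64/115.2 = 55.6% |
| 20% | 1.25 | 64/160 = 40.0% | 64/102.4 = 62.5% |
| 30% | 1.43 | 64/140 = 45.7% | 64/89.6 = 71.4% |
| 40% | 1.67 | 64/120 = 53.3% | 64/76.8 = 83.3% |

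**Step 4: choice of numerator.** Strictly, Reach counts participants in the intervention, and Group Randomization assigns 2 sites x 2 languages x 8 = 32 patients to R-D1D. The table therefore shows trial enrolment. With 32 as numerator, E = 200 and u = 20%, the two figures are 32/160 = 20.0% and 32/200 = 16.0%. The ratio is again 1.25. The percentage-point gap depends on the numerator; the factor does not.

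**The case against.** **The information is largely collected already.** Reasons for not participating are part of Reach, and the screened ineligible are to be described. This stands as far as it goes: telehealth refusals should be visible to anyone who reads the descriptive results. It does not change the percentage, which is the figure most likely to be quoted.

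**The Reach sentence is a general framework definition, and a condensed article may leave the exact denominator to the full protocol.** It is true that Patient-Level Reach restates no ratio. But Outcomes and Measures presents these definitions as the basis of this study's outcomes, and the article has only one patient eligibility list. The point rests on two rules that are stated, not on a missing detail.

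**The criterion is ordinary.** For a telehealth-only program it is reasonable to require willingness before randomization. This stands in full. The fault lies in carrying the criterion into the Reach denominator, not in the criterion.

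A reader might also infer three stronger things that the article does not support:

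- *Patients with poor internet are filed as ineligible.* The criterion asks for willingness, not access or skill. Adapted R-D1D Intervention provides for testing the connection and device and for instruction over more than one meeting if needed, and Implementation Strategies adds technical assistance. Poor connectivity alone does not fail criterion 5 as written.
- *A later trial will overestimate its recruitment.* It could, if planned from the Reach percentage alone. A trial that kept the same criterion would draw on the same willing pool, and its planners could use the screened-ineligible data.
- *The overstatement is some particular number of percentage points.* Any such number depends on an assumed refusal share, pool size and numerator.

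**Conclusion.** The point holds in a limited form. Followed as written, the two definitions remove telehealth refusals from the Reach denominator, and the Reach percentage is then biased upward as a measure of uptake among otherwise suitable patients. The direction is certain whenever anyone refuses on this ground. The factor is 1/(1-u): 1.11 at an assumed 10% refusal, 1.25 at an assumed 20%, and 1 if nobody refuses. The article gives no basis for choosing u, so the actual size is unknown.

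The conclusion assumes that the word eligible in the Reach definition refers to the listed patient criteria, and that the sites record telehealth refusals as ineligible, as those criteria imply. Enrolment, randomization and the between-group comparisons are not affected. The correction is worth making because it is nearly free and concerns a named outcome.

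**What to change.** - Leave criterion 5 in place as a condition for enrolment.
- In Outcomes and Measures, define the Reach denominator as all patients who meet inclusion criteria 1 to 4 and have no exclusion, whether or not they are willing to use telehealth.
- Count patients who fail only criterion 5 as eligible non-participants for Reach, and log the reason. This works only if criteria 1 to 4 and the exclusions are also recorded for patients who refuse.
- Report the percentage among telehealth-willing patients alongside, so that the figure under the present definition is kept.

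The cost is one sentence in the protocol and one code on the screening log. The main Reach figure will be less favourable if any patients refuse.
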